### 3. Aims and objectives

#### 3.1 Aims

The study will assess the feasibility of the trial protocol qualitatively and quantitatively, and preliminary estimate the add-on efficacy and safety of CHM formula FZHFZY external application to topical urea cream for patients with mild-to-moderate psoriasis vulgaris. Results from the pilot study will optimise the study design.

#### 3.2 Objectives

The pilot trial will have objectives to:

- Assess the feasibility of study setting, eligible criteria, intervention, outcome measurements, participant timeline and recruitment strategies
- Explore the blinding credibility and the acceptability of the trial

- Determine the adequate sample size for a definitive full-scale RCT
- Preliminary estimate the add-on efficacy and safety in the treatment group (FZHFZY+ urea cream) compared to that in the control group (Placebo+ urea cream).
- Obtain detailed qualitative feedback on experience and acceptability of patients who complete the pilot RCT.

#### **4. Trial design**

The FZHFZY Trial consists of two main parts. For the quantitative and qualitative components, we will collect data concurrently and analyse data sequentially, with quantitative data informing our sampling of qualitative interviews for analysis.

- Part 1: This will be a two-arm, parallel, randomised, placebo-controlled, double-blind, pilot trial. In all, sixty eligible participants will be randomised at a 1:1 ratio to receive eight weeks' treatment of either CHM FZHFZY granules as a bath therapy plus 10% urea cream, or placebo granules plus 10% urea cream, with a 12-week follow-up phase.
- Part 2: This will be an embedded qualitative study with the above-mentioned pilot RCT. The primary source of data collection will be semi-structured interviews via face to face. The data will be analysed through thematic analysis.

#### **5. Part 1: The pilot RCT**

The procedure of the pilot RCT is presented in Figure 1 and the schedule of events is provided in Table 1.

[figure not shown]

1 Safety assessment: Electrocardiograms, blood (two 4 ml-EDTA tubes and two drying tubes) and urine (one 10 ml-urine tube)

2 biological specimens: blood (three 4 ml-EDTA tubes, three 4 ml-procoagulant tubes, and one 2.5 ml-BD tube), urine (two 10 ml-urine tubes), skin flora (four microtubes), feces (three feces tubes) and oral flora (two microtubes)

3 Safety assessment: blood (two 4 ml-EDTA tubes and two drying tubes) and urine (one 10 ml-urine tube)

4 biological specimens: blood (three 4 ml-EDTA tubes, three 4 ml-procoagulant tubes, and one 2.5 ml-BD tube), urine (two 10 ml-urine tubes), and skin flora (four microtubes)

**Figure 1** Flowchart of the trial procedure

**Table 1** Schedule for research activities, interventions and data collection.

|                                                        | Before
Week 0
(wash-out) | Week 0
(Baseline)                                                               | Week 2 | Week 4 | Week 6 | Week 8 | Week 12                                                                             | Week 16 | Week 20 |
|--------------------------------------------------------|--------------------------------|------------------------------------------------------------------------------------|--------|--------|--------|--------|-------------------------------------------------------------------------------------|---------|---------|
| Research activities                             |                                |                                                                                    |        |        |        |        |                                                                                     |         |         |
| Informed consent                                       | X                              |                                                                                    |        |        |        |        |                                                                                     |         |         |
| Assess eligibility                                     | X                              | X                                                                                  |        |        |        |        |                                                                                     |         |         |
| ECG, blood test, urine test for eligibility assessment |                                | X                                                                                  |        |        |        |        |                                                                                     |         |         |
| Randomisation                                          |                                | X                                                                                  |        |        |        |        |                                                                                     |         |         |
| Treatment: CHM/placebo plus urea cream                 |                                | [figure not shown] |        |        |        |        |                                                                                     |         |         |
| Follow-up                                              |                                |                                                                                    |        |        |        |        | [figure not shown] |         |         |
| Photos taken for representative skin lesions           |                                | X                                                                                  | X      | X      | X      | X      | X                                                                                   | X       | X       |
| Dispense (D)/Collect (C) trial drugs                   |                                | D                                                                                  | C/D    | C/D    | C/D    | C      |                                                                                     |         |         |
| Dispense (D)/Collect (C) home diary record sheet       |                                | D                                                                                  | C/D    | C/D    | C/D    | C/D    | C/D                                                                                 | C/D     | C       |
| Data collection: general information            |                                |                                                                                    |        |        |        |        |                                                                                     |         |         |
| Demographics                                           | X                              | X                                                                                  |        |        |        |        |                                                                                     |         |         |
| Medical history                                        | X                              | X                                                                                  |        |        |        |        |                                                                                     |         |         |
| Concomitant medication                                 | X                              | X                                                                                  | X      | X      | X      | X      | X                                                                                   | X       | X       |
| Data collection: efficacy assessment            |                                |                                                                                    |        |        |        |        |                                                                                     |         |         |
| PASI                                                   | X                              | X                                                                                  | X      | X      | X      | X      | X                                                                                   | X       | X       |
| BSA                                                    | X                              | X                                                                                  | X      | X      | X      | X      | X                                                                                   | X       | X       |
| 7-point sPGA                                           |                                | X                                                                                  | X      | X      | X      | X      | X                                                                                   | X       | X       |

|                                         |  |                                                                                    |   |   |   |   |   |   |   |
|-----------------------------------------|--|------------------------------------------------------------------------------------|---|---|---|---|---|---|---|
| Itch VAS                                |  | X                                                                                  | X | X | X | X | X | X | X |
| DLQI                                    |  | X                                                                                  |   |   |   | X |   |   | X |
| Skindex-16                              |  | X                                                                                  |   |   |   | X |   |   | X |
| Data collection: safety assessment      |  |                                                                                    |   |   |   |   |   |   |   |
| Vital signs                             |  | X                                                                                  |   |   |   | X |   |   | X |
| Physical examination                    |  | X                                                                                  |   |   |   | X |   |   | X |
| Blood test, Urine test                  |  |                                                                                    |   |   |   | X |   |   | X |
| Reporting AEs                           |  | [figure not shown] |   |   |   |   |   |   |   |
| Data collection: feasibility assessment |  |                                                                                    |   |   |   |   |   |   |   |
| Trial medication usage check            |  |                                                                                    | X | X | X | X |   |   |   |
| Blinding credibility                    |  |                                                                                    |   | X |   | X |   |   | X |
| Acceptability                           |  |                                                                                    |   |   |   | X |   |   | X |
| Data collection: biological specimens   |  |                                                                                    |   |   |   |   |   |   |   |
| Blood, urine, Skin microbiota           |  | X                                                                                  |   |   |   | X |   |   | X |
| Stool and Oral cavity microbiota        |  | X                                                                                  |   |   |   |   |   |   |   |

Note: AE, adverse event(s); BSA, Body Surface Area; DLQI, Dermatology Life Quality Index; ECG, electrocardiograms; PASI, Psoriasis Area and Severity Index; sPGA, static Physician's Global Assessment; VAS, visual analogue scale.

### 5.1 Setting and participants

This RCT will be conducted at the Guangdong Provincial Hospital of Chinese Medicine (GPHCM), Guangzhou, China. The GPHCM is one of the largest Chinese medicine hospital with the largest number of annual outpatients and the most powerful hospital in China. There are over 2,000 patients with psoriasis vulgaris visiting the dermatology outpatient clinic at the GPHCM annually. Patients with mild-to-moderate psoriasis vulgaris will be recruited through the poster advertisement and face-to-face consultation. Potential participants may also be recommended to contact the researcher by their physicians (general practitioner, dermatologist or immunologist). Eligible participants will be included in the study after providing written informed consent. The selection criteria are as follows.

#### 5.1.1 Inclusion criteria

- Clinically diagnosed as psoriasis vulgaris [37]
- PASI < 10 or BSA < 10% [7, 38]
- Age between 18 and 65 years
- Written informed consent is provided.

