### 5.6.2 Efficacy outcomes

#### 5.6.2.1 Primary outcome

- Mean change in the PASI total score from baseline to week 8 and week 20 respectively [45]

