#### 5.6.2.2 Secondary efficacy outcomes

- The PGA response, defined as a PGA score of 0 (clear) or 1 (almost clear) and a decrease from baseline at least 2 points on the 7-point static PGA at week 8 and week 20 respectively [46]
- The percentage of patients who achieve at least 75% improvement in PASI score from baseline (PASI-75) to week 8 and week 20 respectively [47]
- The percentage of patients who achieve at least 50% improvement in PASI score from baseline (pasi-50) to week 8 and week 20 respectively [47]
- The mean change in the percent of total BSA affected by psoriasis from baseline to week 8 and week 20 respectively [45]
- The mean change in the total itch VAS from baseline to week 8 and week 20 respectively [48]
- The mean change in the DLQI total score from baseline to week 8 and week 20 respectively [49]
- The mean change in the Skindex-16 total score from baseline to week 8 and week 20 respectively [50]
- The relapse rate at week 20, defined as loss of 50% of PASI improvement from baseline in patients who achieve PASI-50 at week 8 [51].

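### Entry sets no minimum severity, but PGA response needs a 2-point fall, so a patient with baseline sPGA 0 or 1 can never count as a responder

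*Protocol*

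**What the plan says.** Section 3.1 states the aim "for patients with mild-to-moderate psoriasis vulgaris", and section 5.1 says "Patients with mild-to-moderate psoriasis vulgaris will be recruited through the poster advertisement and face-to-face consultation". Section 5.1.1 turns this into two disease criteria: "Clinically diagnosed as psoriasis vulgaris" and "PASI < 10 or BSA < 10" per cent. The synopsis repeats the severity rule. No other inclusion or exclusion criterion limits psoriasis severity in either direction, and sPGA is not an entry criterion.

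Section 5.6.2.2 lists PGA response first among the secondary efficacy outcomes, "defined as a PGA score of 0 (clear) or 1 (almost clear) and a decrease from baseline at least 2 points" on a 7-point static scale, at weeks 8 and 20. The synopsis gives the same definition.

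Table 1 places an eligibility assessment, randomisation and the first sPGA reading all at week 0. Section 5.6.1 says the pilot is to help fix the primary outcome of the full-scale trial and to supply data for its sample size.

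**The concern.** The entry rule and the response definition do not fit together at the mild end. A responder must have room to fall 2 points, but the entry rule does not ensure that room exists. Any patient enrolled almost clear is a certain non-responder in either arm.

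The pilot is meant to inform the choice of primary outcome and the size of the next trial. Certain non-responders lower both arms' response rates and narrow the difference between them, so PGA response would look a weaker candidate endpoint than it is among patients able to meet it. A sample size built on those rates would be larger than a trial with a baseline floor needs.

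**Working it through.** **The plan's own figure.** Section 5.9.1 gives 60 patients, from at least 50 with 15% loss: 50 / (1 − 0.15) = 58.8, so 59, which is consistent with 60. This number is not derived from an effect size, so the present point does not change it.

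**Step 1: who can respond.** Score 0 is clear and 1 is almost clear (section 5.6.2.2). A 7-point scale in unit steps then runs from 0 to 6. For baseline b and final score e, response needs e ≤ 1 and b − e ≥ 2.

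| Baseline sPGA | Final scores that count as response |
|---|---|
| 0 | none |
| 1 | none |
| 2 | 0 only |
| 3 to 6 | 0 or 1 |

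**Step 2: effect on the rates.** Let f be the share entering at sPGA 0 or 1, equal in expectation across arms because of randomisation. Let p1 and p2 be the response rates among patients able to respond.

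- Observed rate in each arm = (1 − f) × p + f × 0 = (1 − f)p, so the ceiling is 1 − f.
- Observed difference = (1 − f)(p1 − p2).

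The protocol gives neither f nor the rates. With an assumed difference of 20 points:

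- f = 0: 20 × 1.0 = 20 points
- f = 10% (6 of 60 patients): 20 × 0.9 = 18 points
- f = 20% (12 of 60 patients): 20 × 0.8 = 16 points

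**Step 3: what this could do to a later sample size.** Assumptions: rates of 40% and 15% among patients able to respond, and 80% power. The two-sided 0.05 level is from section 5.9.2. With p̄ the mean of the two observed rates, the patients needed per arm are

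n = [1.960 √(2p̄(1 − p̄)) + 0.842 √(p1(1 − p1) + p2(1 − p2))]² / (p1 − p2)²

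| f | Observed rates | Difference (points) | n per arm |
|---|---|---|---|
| 0 | 40% v 15% | 25.0 | 49 |
| 10% | 36% v 13.5% | 22.5 | 57 |
| 20% | 32% v 12% | 20.0 | 67 |
| 30% | 28% v 10.5% | 17.5 | 79 |

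At f = 0 the numerator is (1.238 + 0.510)² = 3.055, and 3.055 / 0.0625 = 48.9, so 49.

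**Step 4: the upper end, for clarification only.** Under *or*, only patients over both limits are kept out.

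| PASI | BSA | Eligible under *or* | Eligible under *and* |
|---|---|---|---|
| 5 | 5% | yes | yes |
| 5 | 40% | yes | no |
| 15 | 5% | yes | no |
| 15 | 40% | no | no |

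So one measure may exceed its limit without bound if the other is met. This is what the wording permits. It does not show what was intended.

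**The case against.** The best counter-argument is that f may be negligible. An almost-clear patient would have to complete the washout, bathe daily for eight weeks and attend eight visits, and few may volunteer. This stands, and it is why the range starts at zero. In addition, PGA response is one of eight secondary outcomes in a pilot, and testing the eligibility criteria is itself an objective in section 3.2. Baseline sPGA will be recorded, so f will be known at the end. If the full trial kept the same entry rule, the diluted rates would be the right input for that population. All of this limits the size of the point. It does not remove the mismatch, which follows from the definitions before any patient is enrolled.

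A reader might infer three stronger things.

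- *The sample would not be mild-to-moderate, and the rule should read* and. The documents do not support this. The cited rule is the protocol's only working definition of mild-to-moderate, no section contradicts it, and its sources cannot be checked here. A missing minimum does not conflict with the word mild either.
- *The primary outcome is compromised, because a low baseline PASI limits how far PASI can fall.* The bound is real, but it applies to any such change score and to both arms, and the protocol offers nothing from which to size it.
- *The PGA contrast will lose 2 to 4 points.* That holds only if 10% to 20% of patients enter at sPGA 0 or 1, for which the protocol gives no basis.

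**Conclusion.** The point holds in a limited form. From the protocol's text alone, a patient with baseline sPGA 0 or 1 is eligible if the other criteria are met and cannot be a PGA responder, while baseline 2 requires complete clearance. The only assumption in this is that the scale runs from 0 to 6 in unit steps.

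The size is conditional: the ceiling and the risk difference both scale by 1 − f, with no loss at f = 0. Both f and the response rates used above are assumed. The effect is on a secondary endpoint and on what the pilot can say about it for the next trial. The planned 60 patients are unaffected, and no effect on the primary PASI outcome has been quantified. The use of *or* between the two limits is a matter for clarification and not a demonstrated error.

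**What to change.** Choose one of two routes and state it before data are seen.

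1. Add to section 5.1.1 and the synopsis a requirement of sPGA at least 2 at the week 0 eligibility check, with sPGA recorded before randomisation. Table 1 already has both assessments at that visit, so no visit or test is added.
2. Keep entry as it is and define the PGA response analysis in sections 5.6.2.2 and 5.9.2 as restricted to patients with baseline sPGA of at least 2, reporting how many are left out. Membership is fixed by a pre-treatment value, so the comparison between arms stays randomised.

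The cost is somewhat fewer eligible patients under the first route, or fewer analysed under the second. Section 5.1 reports over 2,000 psoriasis vulgaris patients a year for 60 places, although that count covers all severities. Neither route changes the fact that a patient starting at 2 must clear completely. The sponsor should accept that knowingly.

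Separately, ask the sponsor to confirm in section 5.1.1 and the synopsis whether a patient must be under both limits or only one. If one is enough, a sentence should say how a patient over the other limit is regarded as mild-to-moderate.

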#### 5.1.2 Exclusion criteria

- Currently are pregnant and lactating patients
- Currently have uncontrolled or severe diseases, such as cardiovascular, respiratory, digestive, urinary, haematological or psychiatric diseases; have any known malignancy or a history of malignancy
- Are allergic to the medications used in this study
- Currently are participating in or have participated in other clinical trial(s) in the previous month
- Not complete a wash-out period of psoriasis therapies (see Table 2 for detailed washout requirements of each therapy).

**Table 2** Psoriasis therapies and washout requirements.

| Therapies                                                                                                                                                                                                                                                                                                                                                                                                                                                 | Washout requirements |
|-----------------------------------------------------------------------------------------------------------------------------------------------------------------------------------------------------------------------------------------------------------------------------------------------------------------------------------------------------------------------------------------------------------------------------------------------------------|----------------------|
| Topical agents: Glucocorticoids, Calcineurin inhibitors (e.g. Tacrolimus, Pimecrolimus), Vitamin D analogues (e.g. Calcipotriol, Tacalcitol), Retinoids (e.g. tazarotene), combination treatments (eg. Compound Clobetasol Propionate, Carpotriol betamethasone), Keratin promoter (e.g. 2% – 5% coal tar, 3% salicylic acid, 0.1% – 0.5% anthralin, 5% ichthammol), Keratolytic (e.g. 5% – 10% salicylic acid, 0.1% Retinoids), anthralin, and so on [7] | Two weeks            |
| Antimicrobials; Systemic nonbiologic therapies: methotrexate, cyclosporine, acitretin, azathioprine, leflunomide, Mycophenolate Mofetil and so on; Phototherapies: NB-UVB, PUVA, 308 Excimer                                                                                                                                                                                                                                                              | Four weeks           |

|                                                                                                                                                                                                                   |                           |
|-------------------------------------------------------------------------------------------------------------------------------------------------------------------------------------------------------------------|---------------------------|
| laser and so on [13, 39, 40]                                                                                                                                                                                      |                           |
| Biologics and their half-lives approved by China now [41]:
Etanercept 3.5 days, Infliximab 10 days, Adalimumab 14 days,
Ustekinumab 21 days, Guselkumab 18 days, Secukinumab 27 days,
Ixekizumab 13 days | Five times half-life [42] |

